#### 6.4.2 Power Calculations for Evaluation of Immune Responses

The tables presented in the previous section for evaluation of safety response, are also applicable to the evaluation of immune response (e.g., seroconversion). **Table 6-1** gives the probabilities of observing no subjects with immune response or at least 2 subjects with immune response over a range of underlying response rates. **Table 6-2** gives the exact 95% confidence intervals over a range of observed response rates for each Study Group.

#### 6.4.3 Power Calculations for Primary Immunogenicity Comparisons

The primary immunogenicity objective is to compare the frequency and magnitude of the 2012/13 influenza vaccine strain-specific HAI response at 3 weeks after the ATIV boost in Group 1 to 3 weeks after the ATIV prime in Group 3, as well as to compare the same responses at 3 weeks after the TIV boost in Group 2 to 3 weeks after the TIV prime in Group 4. Each of these comparisons will be made for the 3 strains in the 2012/13 vaccines, so a total of six comparisons will be made for the two primary immunogenicity endpoints, seroconversion and GMT.

**Table 6-3** gives the power to detect a difference in the seroconversion using Fisher's exact test with Type I error of 5% over a range of possible seroconversion rates. **Table 6-4** presents the minimum difference in seroconversion rates that can be detected with 55 or 50 subjects in each Study Group using Fisher's exact tests with 80% power and 5% Type I error rate.

**Table 6-3: Power to Detect Difference in Response Rates between Two Study Groups by Fisher's Exact Test**

| Seroconversion Rate |                   | Power (%) |      |
|---------------------|-------------------|-----------|------|
| Comparator Group    | Prime-Boost Group | N=55      | N=50 |
| 0.4                 | 0.6               | 46        | 46   |
|                     | 0.7               | 85        | 83   |
|                     | 0.8               | 99        | 98   |
|                     | 0.9               | >99       | >99  |
|                     |                   |           |      |
| 0.5                 | 0.7               | 49        | 46   |
|                     | 0.8               | 89        | 85   |
|                     | 0.9               | >99       | 99   |
|                     |                   |           |      |
| 0.6                 | 0.8               | 56        | 51   |
|                     | 0.9               | 95        | 93   |
|                     |                   |           |      |
| 0.7                 | 0.9               | 68        | 64   |

**Table 6-4: Minimum Detectable Difference in Response Rates with 80% Power**

| Comparator Group | Minimum Detectable Difference |      |
|------------------|-------------------------------|------|
|                  | N=55                          | N=50 |
| 0.40             | 0.28                          | 0.29 |
| 0.50             | 0.27                          | 0.28 |
| 0.60             | 0.25                          | 0.26 |
| 0.70             | 0.22                          | 0.23 |
| 0.80             | 0.18                          | 0.19 |

The calculations in this section are presented for the primary immunogenicity comparisons, but are also applicable to comparisons of seroconversion between any two Study Groups, as well as comparisons of proportion of subjects with four-fold increase in neutralizing antibodies, positive anti-stem antibodies, or positive HA specific T-Cell response.

## 6.5 STATISTICAL ANALYSIS

Study enrollment is defined in this protocol as being randomized and receiving the first study vaccination. All enrolled subjects will receive at least one vaccination and therefore will provide some safety data, and be included in the safety analysis.

All statistical analyses will be performed using Statistical Analysis System (SAS) or R statistical software.

A significance level of  $\alpha = 0.05$  will be used for all analyses; no formal multiple comparison adjustments will be employed for safety endpoints or secondary endpoints.

#### 6.5.1 Analysis Variables

The analysis variables consist of baseline characteristics, safety, reactogenicity, and immunogenicity variables.

#### 6.5.2 Baseline Characteristics

Baseline characteristics including demographics and laboratory measurements will be summarized using descriptive statistics.

#### 6.5.3 Safety Analysis

**Reactogenicity:** The number and percentage of subjects experiencing each type of reactogenicity sign or symptom will be tabulated by severity. For a given sign or symptom, each subject's reactogenicity will be counted once under the maximum severity for all assessments.

**Adverse Events:** Adverse Events (AEs) will be coded into Medical Dictionary for Regulatory Activities (MedDRA) preferred terms. The number and percentage of subjects experiencing each specific adverse event will be tabulated by severity and relationship to study product. For the calculations in these tables, each subject's adverse event will be counted once under the maximum severity or strongest recorded causal relationship to study product.

A complete listing of AEs for each subject will provide details including severity, relationship to study product, onset, duration and outcome.

**Safety Laboratory Values:** Safety laboratory values will be summarized as the mean change from baseline along with 95% confidence interval at each timepoint measured in the study. Boxplots of safety laboratory values will be generated for baseline values and for values measured during the course of the study.

#### 6.5.4 Analysis of Immune Responses

The primary analysis for immunogenicity will employ the intent-to-treat (ITT) principle, i.e., all data from enrolled subjects will be used, and subjects will be analyzed according to the study regimen to which they were randomized regardless of the product(s) received. If there are cases of a subject receiving a regimen different from the randomized assignment or subjects who did not complete the prime-boost regimen, then per-protocol analysis may also be performed, according to actual study product received and excluding subjects who did not complete the prime-boost regimen.

The frequency of immune response will be analyzed by tabulating the seroconversion (proportion of subjects with either a pre-vaccination strain-specific HAI titer  $<1:10$  and a post-vaccination HAI titer  $\geq 1:40$  or a pre-vaccination HAI titer  $\geq 1:40$  and a minimum four-fold rise in post-vaccination HAI antibody titer) and exact 95% confidence intervals for each study group. The magnitude of immune response will be analyzed by tabulating the geometric mean titer for each study group. The immune response may also be summarized separately for each age

subgroup. Fisher's exact tests will be used to compare seroconversion between any two study groups.

Missing responses will be assumed to be missing at random, i.e., conditional on the observed data the missingness is independent of the unobserved responses, no imputations for missing data will be made.

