#### 3.1 PRIMARY OBJECTIVES:

- To evaluate the safety and tolerability of each vaccination schedule
- To evaluate the safety and tolerability of concurrent administration of the HA DNA vaccine and either ATIV (FLUAD) or TIV (AGRIFLU) administered in different arms on the same day
- To compare the frequency and magnitude of the 2012/13 influenza vaccine strain-specific HAI response at 3 weeks after the ATIV boost in Group 1 to 3 weeks after the ATIV prime in Group 3, as well as to compare the same responses at 3 weeks after the TIV boost in Group 2 to 3 weeks after the TIV prime in Group 4.

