#### **4.2.6 Concomitant Medications and Procedures**

Current concomitant medications are recorded in the study database at enrollment. Concomitant medications will be updated in the study database if there is an occurrence of an adverse event that requires expedited reporting. Treatment for influenza with antiviral drugs will be recorded on an Influenza Endpoint Case Report Form. Sites should work with study subjects with regard to the timing of FDA-approved vaccines such that, when possible, they should be scheduled at least 14 days before or at least 28 days after a study vaccination. Receipt of a licensed vaccine at any time is not a protocol violation. Vaccinations received during study participation will be recorded in the study database. Otherwise, a record of concomitant medication changes throughout the study will not be recorded in the study database.

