### 6.3.2 Primary Endpoint: Immune Response

For all immunogenicity endpoints, seroconversion is defined as the proportion of subjects with either a pre-vaccination strain-specific HAI titer  $<1:10$  and a post-vaccination HAI titer  $\geq 1:40$  or a pre-vaccination HAI titer  $\geq 1:40$  and a minimum four-fold rise in post-vaccination HAI antibody titer.

- Seroconversion for each of the 2012/13 influenza vaccine strains at 3 weeks after completion of the HA DNA prime-boost regimens (Group 1 and Group 2), or 3 weeks after the ATIV or TIV prime (Group 3 and Group 4)
- Geometric Mean HAI Titer for each of the 2012/13 influenza vaccine strains at 3 weeks after completion of the HA DNA prime-boost regimens (Group 1 and Group 2), or 3 weeks after the ATIV or TIV prime (Group 3 and Group 4)

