#### 6.5.5 Interim Analyses

**Safety Reviews:** The protocol safety review team will review safety data routinely throughout the study. The study will utilize both electronic database features and reviews by designated safety review personnel to identify in a timely manner if any of the safety pause rules of the study are met.

**Immunogenicity Review:** The analyses of immunogenicity may be performed when the HAI assays at 3 weeks after the ATIV or TIV injections in Groups 1 and 2 and the HAI assays at 3 weeks after the prime ATIV or TIV injections in Groups 3-6 have been completed for the study, which may occur prior to completion of safety follow-up visits or collection of data for secondary and exploratory immunogenicity endpoints. Such an analysis would constitute the final analysis for the primary immunogenicity endpoint, so sample size adjustments are not required. Reports providing results by study group may be provided to VRC solely for the purpose of informing decisions related to future trials in a timely manner. The results should in no way influence the conduct of the VRC 703 trial in terms of early termination or later safety or immunogenicity endpoint assessments. Analyses secondary and exploratory immunogenicity assays may also be performed as data are available.

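### The per-protocol rule in 6.5.4 makes a Week 3 comparator titer in Groups 3 and 4 depend on a boost due about 41 weeks later

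*Protocol*

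**What the plan says.** Section 6.5.4 states the analysis sets: "The primary analysis for immunogenicity will employ the intent-to-treat (ITT) principle". If any subject received the wrong regimen or did not finish the regimen, "then per-protocol analysis may also be performed", "according to actual study product received and excluding subjects who did not complete the prime-boost regimen". Non-completion is the only exclusion stated, and it is worded identically for all groups.

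The primary contrasts in Section 3.1 compare "3 weeks after the ATIV boost in Group 1 to 3 weeks after the ATIV prime in Group 3" and "3 weeks after the TIV boost in Group 2 to 3 weeks after the TIV prime in Group 4". Section 6.3.2 repeats these times for seroconversion and geometric mean titer. Table 4-1 and Appendix III put the second injection at Week 16 in Groups 1 and 2 and at Week 44 in Groups 3 to 6.

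Section 6.5.5 lets the immunogenicity analysis run once the three-week assays are complete, before follow-up ends: "Such an analysis would constitute the final analysis for the primary immunogenicity endpoint".

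**The concern.** Completion means different things in the two arms of each primary contrast. In Groups 1 and 2 it is settled before the primary sample, so excluding non-completers is ordinary per-protocol selection. In Groups 3 and 4 it is settled long after the primary titer exists, by an injection that cannot change that titer.

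The later loss need not be random. Vaccination is open-label, and Section 4.4.1 lists refusal of the second injection, a contraindication and investigator judgement as reasons to stop. It also does not permit the ATIV boost in pregnancy, while TIV is not contraindicated. A pregnancy before Week 44 could therefore remove a Group 3 subject, but not necessarily a Group 4 subject, from an analysis of Week 3 titers. If willingness to be boosted is related to the reaction to the prime, and that reaction to the antibody response, the comparator rate is distorted in the very analysis meant to support the intent-to-treat result.

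**Working it through.** **Inputs.** From Table 4-1 and Appendix III: boost at Week 16 (Day 112) in Groups 1 and 2 and at Week 44 (Day 308) in Groups 3 and 4. The primary sample is at Week 19 (Day 133) and Week 3 respectively. Visit windows are from Appendix III. There are 55 subjects per group.

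**Timing of completion against outcome.**
- Groups 1 and 2: boost at Week 16, sample at Week 16 + 3 = 19. Completion precedes the outcome by 3 weeks.
- Groups 3 and 4: 44 - 3 = 41 weeks after the outcome (308 - 21 = 287 days). With windows of +7 days on the Week 3 visit and ±7 days on the boost, the range is (301 - 28)/7 = 39 to (315 - 21)/7 = 42 weeks.
- Two inconsistencies elsewhere do not change the point. Schedule B labels Week 3 as Day 28, which gives (308 - 28)/7 = 40 weeks. Section 6.1 gives a 40-week interval for the concurrent-administration regimens; applied here, it would give 40 - 3 = 37 weeks.

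**Can the set be formed at the time of analysis?** A prime on 1 to 31 August 2012 plus 133 days puts the Group 1 and 2 sample between 12 December 2012 and 11 January 2013, before windows. Groups 3 and 4 are primed in October or November 2012 and sampled three weeks later. Their boost is planned for August 2013. The primary assays could therefore be complete months before completion is known for any Group 3 or 4 subject.

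**Number affected.** The protocol gives no rate for subjects who have a Week 3 titer but miss the Week 44 boost. Assuming 5%, 10% or 15%: 55 × 0.05 = 2.8, 55 × 0.10 = 5.5, 55 × 0.15 = 8.3, or about 3 to 8 per comparator group.

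**Power.** Exact enumeration of Fisher's test (two-sided 5%) reproduces Table 6-3. For 0.4 against 0.7 it gives 84.6% and 82.9% (stated 85 and 83). For 0.7 against 0.9 it gives 68.2% and 64.0% (stated 68 and 64). All 18 entries checked agree within one point. If only the comparator shrinks, power for 0.4 against 0.7 is 84.9% at 55 against 50 and 85.9% at 55 against 47, compared with 84.6% at 55 against 55. The small rises come from the discreteness of the test. Power is not the issue.

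**Outer bounds on the selection effect.** Take the lowest comparator rate in Table 6-3, 0.40 × 55 = 22 responders.
- Drop 3: (22 - 3)/52 = 37% if all were responders, 22/52 = 42% if none were.
- Drop 8: (22 - 8)/47 = 30% if all were responders, 22/47 = 47% if none were.

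These are extremes, not estimates. They show that the direction is unknown and that the shift could reach several points.

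**The case against.** The strongest reply is that the term prime-boost regimen may mean only the HA DNA schedules. Section 6.3.2 attaches it to Groups 1 and 2, Section 6.2 sets it against TIV or ATIV alone, and Table 6-3 contrasts a prime-boost group with a comparator group. On that reading nobody in Groups 3 and 4 is excluded for missing Week 44, and 6.5.5 makes sense. The ambiguity is genuine. But Table 4-1 labels the Group 3 and 4 injections prime and boost, the Introduction describes them as an injection followed by a boost, and 6.5.4 does not limit the rule. The broader reading is the plain one.

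Second, the analysis is optional and supportive. That stands. A reader might infer that the primary result is biased; it is not, because the Week 3 titers stay in the intent-to-treat analysis.

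Third, a reader might take the 10% drop-out in Section 6.4 as the share discarded despite valid Week 3 data. It is not that: it reduces the planning size to 50 and says nothing about who misses only the late boost.

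Fourth, a reader might infer that the protocol deliberately keeps Group 1 and 2 subjects who had influenza or an outside influenza vaccine before their sample. The text is merely silent, and a statistical analysis plan may add such exclusions. The exposure time does differ (19 weeks against 3), but for that same reason excluding these subjects would itself select on post-randomisation events over unequal windows. No figure for the resulting shift can be drawn from the protocol.

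**Conclusion.** The point holds for the per-protocol analysis. As plainly read, 6.5.4 conditions the comparator arm of both primary contrasts on an event about 41 weeks after the outcome, and the rule cannot be applied if the final primary analysis is run before the boost. This is a stated rule that works badly, so an analysis plan would have to override it rather than fill a gap.

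The consequence is limited. The intent-to-treat result is untouched and power is essentially unchanged; the harm is possible selection bias in a supportive analysis. The size of 3 to 8 of 55 per comparator group rests on an assumed 5-15% missing only the late boost.

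One related matter needs reconciling. Inclusion criterion 6 has subjects agree to take seasonal influenza vaccine only from the study site, while Section 4.2.6 says "Receipt of a licensed vaccine at any time is not a protocol violation". These may be meant as a specific and a general statement, but the protocol does not say how they fit together. It would go too far to say that either one is wrong.

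**What to change.** In 6.5.4, tie completion to the endpoint. For the primary contrast, the per-protocol set should be subjects who received every assigned injection due before the primary sample: HA DNA and the boost in Groups 1 and 2, the prime only in Groups 3 and 4. Require both injections only for the post-boost endpoints of Groups 3 to 6. The set can then be formed whenever 6.5.5 allows the primary analysis.

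Reconcile inclusion criterion 6 with Section 4.2.6 so that the status of a non-study influenza vaccine is clear.

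Optionally, add a sensitivity analysis without subjects who had a recorded influenza illness or non-study influenza vaccine between Day 0 and the primary sample. Report it with the caveat that the window is 19 weeks in Groups 1 and 2 and 3 weeks in Groups 3 and 4.

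The cost is wording only. Injections, vaccinations received during the study and influenza illness are already recorded.

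### The protocol promises between-group comparisons of GMT, a primary immunogenicity endpoint, but the analysis it states is a table of group GMTs with no contrast and no interval

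*Protocol*

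**What the plan says.** Section 3.1 sets the primary immunogenicity objective: "To compare the frequency and magnitude of the 2012/13 influenza vaccine strain-specific HAI response at 3 weeks after the ATIV boost in Group 1" with the response after the ATIV prime in Group 3, and likewise for TIV in Group 2 against Group 4.

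Section 6.3.2 lists two primary immunogenicity endpoints. One is seroconversion. The other is "Geometric Mean HAI Titer for each of the 2012/13 influenza vaccine strains at 3 weeks after completion of the HA DNA prime-boost regimens", or after the single ATIV or TIV prime in Groups 3 and 4.

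Section 6.4.3 repeats the objective, notes three strains per contrast, and states that "a total of six comparisons will be made for the two primary immunogenicity endpoints, seroconversion and GMT".

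Section 6.5.4 then gives a method for each endpoint:
- Seroconversion is tabulated with "exact 95% confidence intervals for each study group", and "Fisher's exact tests will be used to compare seroconversion between any two study groups".
- For GMT the full statement is: "The magnitude of immune response will be analyzed by tabulating the geometric mean titer for each study group".

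The power material for these comparisons is Table 6-3, headed "Power to Detect Difference in Response Rates between Two Study Groups", and Table 6-4. Both deal with proportions only. Section 6.4 adds that the study does not test a formal superiority or non-inferiority hypothesis.

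**The concern.** A table of group GMTs puts the two numbers of each contrast on the page, but it neither estimates the difference between them nor says how precisely it is known. The objective is comparative, and so is the hypothesis in Section 4, which expects higher titers from schedules that include HA DNA. An analyst who followed Section 6.5.4 literally would have a comparison with an error measure for frequency and none for magnitude.

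Section 6.5.5 allows these results to be reported early to inform decisions on future trials. A reader of that report would see two GMTs per contrast and could not tell a well-determined ratio from a poorly determined one.

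**Working it through.** **1. Count of comparisons.** Two group pairs (1 vs 3, 2 vs 4) × three strains = 6 per endpoint. Over seroconversion and GMT this is 12. Even if the figure of six is read as a total, the sentence names GMT as one of the endpoints compared.

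**2. Promise against method.**

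| Primary endpoint | Comparison promised (3.1, 6.4.3) | Interval stated (6.5.4) | Between-group method stated (6.5.4) |
|---|---|---|---|
| Seroconversion | yes | exact 95%, per group | Fisher's exact test |
| GMT | yes | none | none |

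No GMT ratio, interval or test appears elsewhere in the protocol. By contrast, Section 6.5.3 attaches a 95% interval even to the mean change in safety laboratory values.

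**3. The protocol's own figures.** No figure is given for GMT, so there is none to reproduce. The seroconversion figures are sound. Exact power of the two-sided Fisher test at 5%, enumerating both binomials, is:

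| Rates | Table 6-3, N=55 / N=50 | Recomputed |
|---|---|---|
| 0.4 vs 0.6 | 46 / 46 | 46.5 / 46.2 |
| 0.5 vs 0.7 | 49 / 46 | 49.1 / 46.3 |
| 0.6 vs 0.8 | 56 / 51 | 56.0 / 51.5 |
| 0.7 vs 0.9 | 68 / 64 | 68.2 / 64.0 |

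Nine of the ten rows were checked and agree within one point; 0.4 vs 0.9 was not run.

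**4. Precision of a GMT ratio at the planned size.** The group sizes, 55 and 50 after about 10% drop-out, come from Section 6.4. The SD of log10 titer is an assumption, because the protocol gives none.

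For two groups of n, the 95% interval is the ratio divided and multiplied by 10^(t × SD × √(2/n)), where t is the 97.5% point on 2n − 2 degrees of freedom. For n = 55 and SD = 0.4, the exponent is 1.982 × 0.4 × √(2/55) = 0.151, and 10^0.151 = 1.42.

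| Assumed log10 SD | Factor, n=55 | Factor, n=50 |
|---|---|---|
| 0.4 | 1.42 | 1.44 |
| 0.5 | 1.55 | 1.58 |
| 0.6 | 1.69 | 1.73 |
| 0.7 | 1.84 | 1.90 |

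For a single group GMT the factor is 10^(t × SD/√n) on n − 1 degrees of freedom. At n = 55 it runs from 1.28 (SD 0.4) to 1.55 (SD 0.7).

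**5. What the table alone would hide.** Suppose, for illustration, that two tabulated GMTs stand in the ratio 1.5. With SD 0.4 the interval is 1.5/1.42 to 1.5 × 1.42, or 1.06 to 2.13. With SD 0.6 it is 1.5/1.69 to 1.5 × 1.69, or 0.89 to 2.54. The first excludes a ratio of 1 and the second does not, yet the two tables would look the same.

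**The case against.** The strongest reply is that the interval and scale for a GMT comparison are ordinary SAP content, that Section 6.5.4 does not say tabulation is all that will be done, and that Sections 3.1 and 6.4.3 already commit the trial to comparing magnitude. Part of this stands. An SAP that is not shown may add a GMT ratio, so the point concerns what this protocol states. It does not dispose of the point. Section 6.5.4 is not silent on GMT: it states how magnitude is analysed, and it does so beside an interval and a named test for the other primary endpoint. That statement falls short of Section 6.4.3, and the two should agree.

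A second reply is that a Phase 1b study without a formal null hypothesis (Section 6.4) may reasonably describe its GMTs. This stands as an argument against adding formal tests or a GMT power table. It is no argument against an interval, because a descriptive comparison still needs an estimate and its precision.

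A reader might infer more: that GMT is the more sensitive endpoint and that most of the information in the sera is lost. The documents do not support this. If seroconversion were a single cut on a normal log fold-rise, a t-test on fold-rise at N=55 would have about 75 to 98% power where Fisher's test has 46 to 68%. But the primary endpoint is post-vaccination titer, which also carries the spread in baseline titer, and the seroconversion rule in Section 6.3.2 depends on baseline. If the post-vaccination SD is assumed to be 1.25 times the fold-rise SD, the range falls to 56 to 88%. At 1.5 times it is 42 to 75%, partly below Fisher's test. No power gain should be claimed.

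**Conclusion.** The point holds as a mismatch inside the protocol. A between-group comparison of GMT is promised for two contrasts and three strains, and the stated analysis supplies neither a contrast nor an interval. This rests on the text alone and needs no assumption about titers.

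Its size can only be indicated. With an assumed log10 SD of 0.4 to 0.7 and 55 per group, each unreported interval would span the ratio divided and multiplied by about 1.4 to 1.8 (1.4 to 1.9 with 50 per group), for an unadjusted two-sample comparison.

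A reader might also conclude that the magnitude question cannot be answered by the trial at all. That goes too far: the sera are collected and the intention to compare is stated. Only the stated analysis falls short. Nor does the gap call for six more tests at the 0.05 level. Apart from Section 6.4, Groups 1 and 2 are randomised before and separately from Groups 3 to 6 (Section 6.5.6), so an unadjusted p-value for 1 vs 3 or 2 vs 4 could look more conclusive than the design allows.

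**What to change.** In Section 6.5.4, state that for each 2012/13 strain and each primary contrast (1 vs 3, 2 vs 4) the ratio of GMTs will be estimated from log-transformed post-vaccination HAI titers, with a 95% confidence interval. Preferably the estimate comes from a linear model with baseline log titer, age stratum and site as covariates. The Day 0 serum is already in the schedule of evaluations, and age and site are the randomisation strata. Add a 95% interval for each group GMT.

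In keeping with Section 6.4, describe these as estimates with their precision rather than as additional formal tests. In Section 6.4.3, say that the six comparisons apply to each of the two endpoints, so that it matches Section 6.5.4.

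The cost is a change of wording in the protocol (and in the SAP, if it follows the same text) and a few more lines of analysis. No new subjects, samples or assays are needed. Adjustment for baseline does not make contrasts across the two randomisations into randomised ones, and the report should say so.

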#### **4.4.1 Discontinuation of Study Injections**

For those who begin a schedule, discontinuation of the injection schedule may occur for the following reasons:

1. Subject declines to receive the second study injection.

2. Circumstances have arisen that constitute a contraindication to administering the vaccine as indicated by the package insert for TIV or the Investigators Brochure for ATIV or as based on the clinical judgment of the IoR or Protocol Chair.
3. The Site IoR assesses that it is not in the best interest of the subject to continue on the vaccination schedule.

Pregnancy is not a contraindication to the licensed TIV, but research blood draws will be adjusted as indicated in **Appendix III**.

ATIV is not licensed in the U.S.; therefore, administration of ATIV to a pregnant subject is not permitted in this protocol. If the ATIV boost is not given due to pregnancy, the subsequent research blood draws should be discontinued. The TIV injection can be offered by the site to subjects who became pregnant on the study as a standard of care.

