## 6.4 **SAMPLE SIZE AND ACCRUAL**

The study is planned to enroll a total of 330 healthy adults stratified by age groups (18-50 and 51-70) to receive one of six vaccine regimens defined in **Table 4-1**. The first 110 subjects enrolled will be randomized with equal allocation to receive 2012/13 HA DNA prime with 2012/13 ATIV boost (Group 1) or 2012/13 HA DNA prime with 2012/13 TIV boost (Group 2). The remaining 220 subjects will be randomized with equal allocation to receive 2012/13 ATIV

with 2013/14 ATIV boost (Group 3), 2012/13 TIV with 2013/14 TIV boost (Group 4), concurrent administration of 2012/13 HA DNA and ATIV with 2013/14 ATIV boost (Group 5), or concurrent administration of 2012/13 HA DNA and TIV with 2013/14 TIV boost (Group 6).

Enrollments may occur rapidly at more than one site. The EMMES Corporation will carefully monitor study enrollment and notify all sites and the VRC Protocol Chair when the completion of enrollment is near in order to end recruitment and to plan how to fairly accommodate, to the degree possible, the enrollment of eligible volunteers that have already been recruited. The decision to stop study enrollments will be made by the VRC Protocol Chair.

This study is not designed to test a formal null hypothesis for superiority or non-inferiority. This section does provide an indication of the power available to observe specific events (e.g., particular adverse events) assuming a range of underlying “true” rates, the precision available in estimating immune response rates, and the power to detect differences in response rates between Study Groups. While drop-out is expected to be low, power calculations assuming approximately 10% drop-out (N=50/per group) are also presented.

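### The plan assumes responses are missing at random given the observed data, but its stated immunogenicity analysis uses only study group, so it needs the stricter condition that missingness is unrelated to response within each group.

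*Protocol*

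**What the plan says.** Section 6.5.4 of the protocol states the assumption: "Missing responses will be assumed to be missing at random". It defines this to mean that, once the observed data are taken into account, whether a response is missing does not depend on its unseen value. It adds that "no imputations for missing data will be made". The analyses it names are "Fisher's exact tests will be used to compare seroconversion between any two study groups" for frequency and "The magnitude of immune response will be analyzed by tabulating the geometric mean titer for each study group" for magnitude. Age subgroups may be summarized separately, but that is optional. The primary analysis is called intent-to-treat: "all data from enrolled subjects will be used, and subjects will be analyzed according to the study regimen to which they were randomized".

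Section 6.5.6 stratifies randomization by clinical site and age. Section 6.3.2 places the primary endpoint 3 weeks after completion of the prime-boost regimen in Groups 1 and 2, and 3 weeks after the first injection in Groups 3 and 4. Appendix III puts these at Week 19 and Week 3.

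Among the reasons for stopping injections, section 4.4.1 lists "Subject declines to receive the second study injection". It also says that when an ATIV boost is withheld because of pregnancy, later research blood draws stop. On loss, section 6.4 expects little drop-out, but "power calculations assuming approximately 10% drop-out (N=50/per group) are also presented".

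**The concern.** Missing at random, as the protocol defines it, lets missingness depend on anything observed: group, age, site, Day 0 titer. An analysis that rests on this assumption has to use those observed variables. A crude proportion or geometric mean among subjects with a sample, compared between groups, uses group alone. If older subjects are both less likely to return and less likely to respond, the assumption holds and the crude estimate is still biased.

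The design makes this relevant to the primary contrasts, Group 1 against 3 and Group 2 against 4. A subject in Group 1 or 2 must stay 19 weeks and come for a second injection to have the primary value as defined. A subject in Group 3 or 4 needs one injection and a visit at Week 3. The pregnancy rule can remove the primary value in Group 1 but not in Group 3, where that value follows the Day 0 injection; such loss is related to sex and age. What is at stake is a modest bias of unknown sign in the primary comparison, with no stated check on it.

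**Working it through.** **1. The plan's own figures.** Exact power of a two-sided Fisher's exact test at 0.05 reproduces Table 6-3 (N=55 / N=50):

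| Rates | Stated | Recomputed |
|---|---|---|
| 0.4 vs 0.6 | 46 / 46 | 46.5 / 46.2 |
| 0.5 vs 0.7 | 49 / 46 | 49.1 / 46.3 |
| 0.6 vs 0.8 | 56 / 51 | 56.0 / 51.5 |
| 0.7 vs 0.9 | 68 / 64 | 68.2 / 64.0 |

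None of these is in dispute. The N=50 column is a loss of 5 in 55, or 9.1%.

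**2. Bias of the crude rate when loss depends on age.** Assumptions, not in the protocol: two age strata of equal size, average loss 10% in the prime-boost group, a complete comparator, and within each stratum missingness unrelated to response. With stratum rates p_young and p_old and losses d_young and d_old, the crude observed rate is

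[(1 − d_young)·p_young + (1 − d_old)·p_old] / [(1 − d_young) + (1 − d_old)]

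and the true rate is (p_young + p_old)/2. The difference simplifies to

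bias = (p_young − p_old)·(d_old − d_young) / [4·(1 − average loss)].

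Example: 0.20 × 0.10 / (4 × 0.90) = 0.0056.

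| Age gap in response (rates) | Loss 5% young, 15% old | Loss 0% young, 20% old |
|---|---|---|
| 20 points (0.8, 0.6) | +0.6 | +1.1 |
| 40 points (0.8, 0.4) | +1.1 | +2.2 |
| 60 points (0.9, 0.3) | +1.7 | +3.3 |

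Reversing which stratum loses more reverses the sign. Equal loss in both strata gives zero, whatever the loss in the other group. The same selective loss in both groups with the same age gap cancels in the difference.

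A simulation of the 20-point gap with 0% and 20% loss gave a crude bias of +1.13 points, and 0.00 after standardizing to the age mix at randomization. Using the observed stratum is therefore what makes the stated assumption sufficient.

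**3. Geometric mean titer.** The same formula on the log scale gives a multiplicative bias of 1.01 to 1.08 for assumed ratios of 1.5 to 4 between the age-stratum geometric means.

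**4. Effect on the test.** With a true rate of 0.6 in both groups and n = 50 against 55, the size of Fisher's test is 4.1% without bias, 4.9% with +2.2 points and 5.7% with +3.3 points.

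**5. A separate, extreme bound.** This is not the bias in step 2. It asks what happens if all 5 missing subjects in one group of 55 failed, or all responded. Against an illustrative complete comparator of 33/55 (60%):

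| Handling of the 5 missing | Rate | Two-sided Fisher p |
|---|---|---|
| Left out | 40/50 = 80% | 0.034 |
| Counted as non-response | 40/55 = 73% | 0.23 |
| Counted as response | 45/55 = 82% | 0.020 |

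**The case against.** Three stronger readings are tempting, and the protocol does not support them.

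- A reader might infer that the analyses are valid only if data are missing completely at random. They do condition on group, so loss may differ freely between groups without bias as long as it is unrelated to response within each group. The Week 19 against Week 3 timing alone is therefore not a bias.
- A reader might infer that subjects who skip the boost drop out of the primary result. Section 4.4 keeps subjects in follow-up whenever possible, and section 6.5.4 excludes non-completers only from the optional per-protocol analysis. The stated exception is the pregnancy rule. What remains is an ambiguity: section 6.3.2 times the endpoint from completion of the regimen, so the primary value of an unboosted subject is not clearly defined.
- A reader might infer that loss favours prime-boost. Nothing in the protocol says who would be lost, and step 2 shows that the sign can go either way.

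The size can also be challenged. The protocol expects little drop-out and applies 10% to every group. In its account of earlier trials (section 1.4.2), 147/149 (99%) and 126/131 (96%) of expected inactivated-vaccine injections were given. The trial is Phase 1b and is not built around a formal hypothesis test. Covariate models and sensitivity analyses are often left to the SAP, which is not at hand.

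Most of this stands and limits the size of the point. It does not remove the mismatch, which lies within section 6.5.4: that section fixes both an assumption and a method, and the first does not justify the second.

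**Conclusion.** The point holds in a limited form. The stated assumption is weaker than the one the stated analysis needs. Under the assumptions in step 2, the resulting bias in a seroconversion rate is about 0.6 to 3.3 points, of unknown direction, against minimum detectable differences of 18 to 29 points in Table 6-4, and the test's size stays near 5%. Stronger dependence, for instance on baseline titer, could give more, but the protocol has no figures from which to judge it.

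The shift from 80% to 73% in step 5 should not be read as the size of this defect. It is a bound for data that are not missing at random, and covariate adjustment would not remove it. Its use is to show that, at the protocol's own planning loss and with all of that loss in one group, a nominally significant comparison can depend on how five subjects are handled. The analysis is not invalid, but it should be improved.

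**What to change.** - Compare log titers by ANCOVA with Day 0 titer, age stratum and site as covariates.
- Compare seroconversion with an analysis adjusted for, or stratified by, age and site. Fisher's exact test can stay as a supportive analysis.
- Do not adjust the between-group contrast for interim titers. In Groups 1 and 2 the Week 3 and Week 16 titers follow the DNA prime, so adjusting for them would remove part of the effect under study. In Groups 3 and 4 the Week 3 titer is the primary outcome itself.
- Add one sensitivity analysis that counts missing primary responses as non-response in all groups.

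The cost is a change of wording in section 6.5.4 or the SAP and a few extra analyses of data already collected. No visit, sample or subject is added.
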